## 16.6 Safety Variables

The following safety assessments are considered as safety endpoints:

- Safety profile of AOP2014 in terms of the incidence of AEs graded according to NCI CTC Version 4.03;
- Autoimmunity induced by AOP2014 in terms of ANA.

## 16.7 Methods of Analysis

The analyses of the primary and secondary efficacy endpoints will be performed for the ITT population. All randomized patients will be analysed within the group they were randomized to, not regarding their actual further treatment. In addition, the confirmatory analysis of the primary endpoint will be performed for the PP population as sensitivity analysis.

### Primary efficacy endpoint

The four hypotheses will be tested in hierarchical order, see above. Null hypotheses 1, 2 and 4 will be tested with the two-sided, uncorrected chi-square test. Null hypothesis 3 will be tested with the two-sided log-rank test. The result of BCR-ABL ratio according to the IS needs to be observed. In case of null hypotheses 1, 2, and 4, the BCR-ABL ratio according to the IS has to be available. For the times 6, 12, and 24 months after stop of TKI (i.e. 7, 13, and 25 months after randomization), a time interval around the corresponding time is allowed. Each result should be relatable to exactly one of the visits scheduled in the protocol. Accordingly, intervals are defined by the time in the middle between two visits (schedule of visits see e.g. study flow chart). As visits are scheduled 6, 7, and 8 months after randomization, the interval for relating a result to the 7-month visit is given by 6.5 to 7.5 months after randomization. With visits planned 11, 13, and 15 months, the interval for relating a result to the 13-month visit is given by 12 to 14 months, and finally, with visits foreseen 24, 25, and 36 months after randomization, the result should be recorded within the interval from 24.5 to 30.5 months after randomization. In case of more than one observation within an interval, the approach of Pffirmann et al. will be chosen in order to determine the decisive result. In case of the observation of an extremely unfavourable result prior to the upper time limit of an interval, this result will be carried forward and will be rated as “no MMR/relapse”. Extremely unfavourable results are accelerated disease, blast crisis, or death from any cause. Details on the outcome will be reported. For analyzing null hypothesis 3, it is important to ensure that the BCR-ABL ratio is evaluated at all times foreseen in Table 1. Accelerated disease and blast crisis imply a prior loss of MMR. Molecular RFS probabilities over time will be described by Kaplan-Meier estimates. RFS probabilities over time will be compared by the log-rank test.

Allogeneic stem cell transplantation in chronic phase or restart of TKI after prior stopping of TKI and without prior loss of MMR will be rated as a drop-out in case this happened prior to an evaluation which would be needed to determine the result for an interval corresponding to hypothesis 1, 2, or 4. In case of hypothesis 3, the observation time of a patient is censored at the time of allogeneic stem cell transplantation or of a restart of TKI without a prior loss of MMR. In this case, the censoring means a loss of information reducing the precision of the estimated probabilities of molecular relapse-free survival but should not alter the estimated probabilities themselves. Accordingly, it is important that the reasons for the reintroduction be clearly stated in any case. Estimated with the Kaplan-Meier method, the probabilities of molecular relapse-free survival describe what to expect, what can be really achieved, if the possibility of a premature TKI restart would not exist.

In case the event “restart of TKI without a prior loss of MMR” has to be regarded as informative with respect to the probabilities of molecular relapse-free survival, the Kaplan-Meier method is not

appropriate. Instead, the cumulative probabilities of a molecular relapse over time have to be estimated by the cumulative incidence function (CIF) 60. The event “restart of TKI without a prior loss of MMR” is then regarded as a competing risk.

Whatever the situation, non-informative or informative censoring, the cumulative incidence function will be calculated (in addition). It will present the cumulative probabilities of a molecular relapse under consideration of the presence of the competing event “restart of TKI without a prior loss of MMR” and also provide an estimation of the probabilities of this competing event itself.

Differences between the treatment strategies prior to discontinuation will be tested by the Gray test (Gray RJ et al., Ann Stat, 1988), if the assumption of non-informative censoring does not hold.

As explorative analyses, depending on the endpoint, multivariate logistic or Cox regression analyses will be performed to analyse the influence of baseline covariates such as the effect of different duration of prior TKI therapy.

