## 16 Statistical Considerations

### 16.1 Hypotheses

Four hypotheses are tested in hierarchical order. To avoid inflation of type 1 error (false rejection of a null hypothesis), further confirmatory testing has to be stopped as soon as a null hypothesis could not be rejected. All four hypotheses are tested at significance level 0.05.

At first,

Null hypothesis 1: “The probability of molecular relapse-free survival (RFS) 7 months after randomization / 6 months after stopping TKI is not different between the two arms A and B”

is tested against the

Alternative hypothesis 1: “The probability of molecular RFS 7 months after randomization / 6 months after stopping TKI is different between the two arms A and B”.

In case null hypothesis 1 can be rejected,

Null hypothesis 2: “The probability of molecular RFS 13 months after randomization / 12 months after stopping TKI is not different between the two arms A and B”

is tested against the

Alternative hypothesis 2: “The probability of molecular RFS 13 months after randomization / 12 months after stopping TKI is different between the two arms A and B”.

In case null hypothesis 2 can be rejected,

Null hypothesis 3: “No difference in the molecular RFS probabilities between the two arms A and B at any time”

is tested against the

Alternative hypothesis 3: “Molecular RFS probabilities between the two arms A and B are different”.

In case null hypothesis 3 can be rejected,

Null hypothesis 4: “The probability of molecular RFS 25 months after randomization / 24 months after stopping TKI is not different between the two arms A and B”

is tested against the

Alternative hypothesis 4: “The probability of molecular RFS 25 months after randomization / 24 months after stopping TKI is different between the two arms A and B”.

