**Table 11 Definitions of Analysis Populations**

### 16.3 Demographic and Other Baseline Characteristics

All demographic characteristics, history of disease, CML baseline characteristics (BCR-ABL ratio,), prior treatment history (TKI treatment duration, type of TKI used, IFN therapy, prior unsuccessful discontinuation attempt), and CML characteristics (Sokal, EURO, EUTOS, and ELTS score at primary CML diagnosis, type of BCR-ABL transcript, cytogenetics at primary CML diagnosis) will be tabulated by treatment group and summary measures will be given for the intention-to-treat (ITT) population.

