## 16.10 Sample Size Calculation

Molecular relapse-free survival (RFS) will be tested at three fixed times, 7, 13, and 25 months after randomization. In arm B, without any treatment after stopping TKI, the probabilities of molecular RFS at 7, 13, and 25 months are assumed to be 55%, 50%, and 45%. At each time, an increase by an absolute value of 20% in arm A is expected. At all three times, confirmatory testing is intended. To avoid an inflation of type I error, the hypotheses are put in hierarchical order. At all times, a power of 80% is planned. It is a characteristic of the binomial distribution that the variance is the higher, the nearer the probabilities are to the level of 50%. Accordingly, sample size estimation needs to be based on the assumptions at 25 months.

Patients in the standard arm B are expected to have a molecular relapse-free survival probability of 45% 24 months after discontinuation of TKI treatment. In the investigational arm A, we expect that the molecular RFS probability after 24 months of discontinuation of TKI can be increased by 20% as compared with the standard arm. Accordingly, 192 patients need to be randomized 1:1 to be able to reject the null hypothesis of same relapse-free survival probabilities with a two-sided uncorrected chi-square test at a significance level of 0.05 and a power of 80%. With an expected drop-out of 10%, the 1:1 randomization of 214 patients is necessary. The sample size calculation was performed with the program “PS Power and Sample Size Calculations”, Version 3.1.2 (Dupont WD et al., Controlled Clin Trials, 1997).

The hierarchical ordering of the hypotheses will be in accordance with the chronological ordering of the times. Assuming that all drop-outs will occur before 6 months (the most adverse case), 192 patients would be ready for analysis. With these 192 patients randomized 1:1, a molecular RFS probability of 55% at 7 months in arm B and of 75% in arm A, we would be able to reject the null hypothesis of same relapse-free survival probabilities with a two-sided uncorrected chi-square test at a significance level of 0.05 with a power of 83%.

With 192 patients randomized 1:1, a molecular RFS probability of 50% at 13 months in arm B and of 70% in arm A, we would be able to reject the null hypothesis of same relapse-free survival probabilities with a two-sided uncorrected chi-square test at a significance level of 0.05 with a power of 81%.

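### The confirmatory tests are valid and reach planned power, but they use no baseline covariate although BCR-ABL level and TKI duration are known before randomization; this may give up some power

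*Protocol*

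**What the plan says.** Section 16.1 sets four hypotheses in a fixed order: "All four hypotheses are tested at significance level 0.05". Section 16.7 (Primary efficacy endpoint) assigns the tests: "Null hypotheses 1, 2 and 4 will be tested with the two-sided, uncorrected chi-square test", and "Null hypothesis 3 will be tested with the two-sided log-rank test". None of the four uses a covariate. Section 16.10 sizes the trial on the unadjusted chi-square test.

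Both covariates are available before randomization. Section 9.2 requires at least three years of TKI treatment and, before randomization, a confirmatory PCR of MR4 or better from a reference laboratory. Section 16.3 lists among the items to be tabulated by arm "CML baseline characteristics (BCR-ABL ratio,), prior treatment history (TKI treatment duration". Neither covariate is a stratification factor; section 6 stratifies by site and prior failed discontinuation.

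Covariates enter section 16.7 only through explorative logistic or Cox models, "to analyse the influence of baseline covariates such as the effect of different duration of prior TKI therapy". TKI duration is the one example given there. The BCR-ABL level is not named in any model. Section 16.11 classes everything beyond the four hypotheses as explorative.

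**The concern.** The endpoint is a threshold on BCR-ABL, and entry admits MR4, MR4.5 and MR5. Baseline depth on the same scale is therefore a natural candidate covariate. Chance imbalance in depth or in TKI duration between arms of about 96 evaluable patients is not controlled by the randomization and not corrected by the tests.

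A pre-specified adjusted analysis of the same risk difference would use data that the trial collects anyway. At stake is some power in a chain where hypothesis 4 is reached only if the first three are rejected, and where hypothesis 4 has no margin above its planned 80%.

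**Working it through.** **Inputs**
- Two-sided level 0.05 per hypothesis (sections 16.1 and 16.7).
- Arm B (section 16.10): "the probabilities of molecular RFS at 7, 13, and 25 months are assumed to be 55%, 50%, and 45" per cent. Arm A: "an increase by an absolute value of 20% in arm A is expected" at each time.
- Target: "At all times, a power of 80% is planned".
- 192 evaluable patients, 96 per arm (section 16.10).
- R², the share of outcome variance that the two covariates explain together. The protocol gives no value. I assume a range from 0 to 0.20.

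**Step 1: the plan's own figures.** With d = 0.20, n per arm and p̄ the mean of the two probabilities,

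power = Φ{[d√n − 1.96√(2p̄(1−p̄))] / √[pA(1−pA) + pB(1−pB)]}.

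- 25 months, 45% v 65%: (1.9596 − 1.3790)/0.6892 = 0.842, power 80.0%.
- 13 months, 50% v 70%: (1.9596 − 1.3579)/0.6782 = 0.887, power 81.3% (stated 81%).
- 7 months, 55% v 75%: (1.9596 − 1.3221)/0.6595 = 0.967, power 83.3% (stated 83%).
- Drop-out: 192/0.9 = 213.3, hence 214.
- Log-rank: with 86 to 89 expected events, three standard approximations give 79% to 83%, in line with the stated value just above 80%.

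All stated figures reproduce.

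**Step 2: power with adjustment.** Adjustment multiplies the variance by about (1 − R²), which is the same as using n = 96/(1 − R²) in the formula. Example for 25 months at R² = 0.10: n = 106.7, 0.20√106.7 = 2.0656, (2.0656 − 1.3790)/0.6892 = 0.996, power 84.0%.

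| R² (assumed) | n per arm, effective | H1, 7 mo | H2, 13 mo | H4, 25 mo | Total N for 80% at 25 mo |
|---|---|---|---|---|---|
| 0 | 96.0 | 83.3% | 81.3% | 80.0% | 192 |
| 0.02 | 98.0 | 84.1% | 82.0% | 80.8% | 190 |
| 0.05 | 101.1 | 85.2% | 83.2% | 82.0% | 184 |
| 0.10 | 106.7 | 87.0% | 85.2% | 84.0% | 174 |
| 0.20 | 120.0 | 90.6% | 89.0% | 88.1% | 154 |

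**Step 3: check by simulation.** 4,000 trials per setting, 96 per arm, one normally distributed covariate and a correctly specified logistic model. Chi-square power against power of the standardized risk difference:
- 7 months: 83.7% v 83.9% (R² 0), 83.1% v 85.3% (0.05), 83.3% v 87.6% (0.10).
- 25 months: 79.8% v 80.1% (R² 0), 80.9% v 83.4% (0.05), 78.7% v 83.1% (0.11).
- Type I error with 55% in both arms: 4.7% to 5.7% adjusted, 4.2% to 5.9% chi-square.

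The simulation error is about √(0.85 × 0.15/4000) = 0.6 points for power. The approximation in step 2 holds, and no loss is visible when the covariate is useless.

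**Step 4: what these R² values require.** For one evenly split binary covariate at 7 months, with pooled RFS 65% and SD √(0.65 × 0.35) = 0.477, the RFS difference between its two levels is √R² × 0.477/0.5. R² = 0.05 needs 0.224 × 0.477/0.5 = 21 points; R² = 0.10 needs 0.316 × 0.477/0.5 = 30 points. Two covariates could share this. An uneven split would need a larger difference.

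No adjusted power was computed for hypothesis 3.

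**The case against.** The strongest reply is that nothing is wrong. An uncorrected chi-square test is a valid test of equal RFS probabilities, it is the test the sample size rests on, and the planned power is met. A simple confirmatory test supported by explorative models is a legitimate choice. All of that stands.

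The gain is also hypothetical. Entry requires MR4 or better on at least three consecutive results, nothing worse in the last year, and at least three years of TKI, which narrows both ranges. Step 4 shows that even R² = 0.05 from a single binary covariate needs an RFS contrast about as large as the 20-point treatment effect. This stands too, and it makes the rows above 0.10 upper values without support in the protocol.

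Three stronger inferences are tempting and do not hold:
- A reader might infer that the unadjusted tests certainly cost power. The loss is zero at R² = 0, and the protocol does not say where R² lies.
- A reader might take section 16.7 to declare TKI duration prognostic. It names duration as an influence to be explored. The background in section 2.2 links depth of remission to relapse risk, but gives no strength within the range eligible here.
- A reader might infer that adjustment can never reduce precision. For a main-effects logistic model in a sample of this size, the evidence supports only that no loss was visible in simulation.

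The objection does not remove the core point: the covariates cost nothing to obtain, the target quantity can be kept, and the choice of unadjusted tests is fixed in the protocol itself.

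**Conclusion.** The point holds as an optional improvement. The confirmatory tests are sound and powered as planned, but they leave unused two baseline values that may be prognostic. If these explain 5% to 10% of the outcome variance, the gain is about 2 to 4 points of power per fixed-time hypothesis, equal to 8 to 18 of the 192 evaluable patients at 25 months (192 − 184 and 192 − 174). With no prognostic strength the gain is nil. The figures rest on the protocol's RFS assumptions, on 96 evaluable patients per arm, and on an R² that is assumed throughout. Severity is low, and so is confidence in the size.

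**What to change.** Before the first interim analysis, amend section 16.7 (and the SAP) as follows.

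- **Hypotheses 1, 2 and 4:** make the primary analysis a standardized (marginal) risk difference from a logistic model with arm, last pre-randomization BCR-ABL and log TKI duration, with robust variance and 95% CI. The marginal risk difference keeps the planned comparison of RFS probabilities; an adjusted odds ratio would change it.
- **Coding of BCR-ABL:** choose categories into which every eligible patient falls, for example detectable v undetectable. A split at MR4.5 does not work for all: section 9.2 admits undetectable disease with at least 10,000 ABL transcripts, while section 9.1 treats samples below 32,000 as inevaluable for MR4.5.
- **Analysis set:** use the same patients as the planned chi-square test. Section 16.7 requires an available result and counts some patients as drop-outs, so standardizing over all 214 randomized patients would add a missing-data assumption.
- **Hypothesis 3:** pre-specify a matching covariate-adjusted Cox test or stratified log-rank test, so that the hierarchy does not mix adjusted and unadjusted primary tests.
- **Retain** the unadjusted tests as sensitivity analyses, and the order and 0.05 level of the hierarchy.

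Prior failed discontinuation, a stratification factor that the tests also omit, has a separate and stronger claim to inclusion and could be settled in the same amendment.

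The cost is wording, slightly more analysis work, and dependence on a pre-specified model. No new data and no change in sample size are needed.

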**Randomization:**

Randomization will be performed centrally by the Coordinating center for Clinical Trials in Marburg. Eligible patients will be randomized in a 1:1 ratio to receive AOP2014 or surveillance by stratified randomization according to the trial site and prior failure of a discontinuation attempt (yes/no).

Screened patients who were not randomized must be registered at KKS Marburg. The reason should be noted on the respective form.

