**Koordinierungszentrum für klinische Studien (KKS)**

**Philipps-University Marburg**

**[name]**

**D-35043 Marburg**

**Monday-Thursday 8.00–16.00 h**

**Friday 08.00–14.00 h**

**[contact]**

**[contact]**

Randomization will not be possible during public holiday.

The randomization of an eligible patient can take place if all inclusion criteria and none of the exclusion criteria are fulfilled. Therefore the investigator completes the study specific randomization form, which is a part of the Investigator's Folder (ISF), and sends it to KKS Marburg *via* fax. In this form the investigator has to fill in also the Patient-ID (Pat-ID). Pat-ID is combined from the site number (2-digit, starting with 01) and a sequencing number of the patients starting with 001 for each site. This unique Pat-ID is used for all documentation on e-CRF and DCF.

KKS Marburg reports the randomization result back to the center.

The chance for randomization to the investigational arm or the standard arm is 1:1. Permuted block randomization will be used, stratified by:

- site
- prior failure of a TKI discontinuation attempt (yes/no)

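### The confirmatory chi-square and log-rank tests ignore the randomisation strata; stratifying them by prior TKI-discontinuation failure is a free gain in efficiency, not a correction of size or sample size

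*Protocol*

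**What the plan says.** **Randomisation.** Section 6 states: "Permuted block randomization will be used, stratified by" site and "prior failure of a TKI discontinuation attempt (yes/no"). The synopsis names the same two factors: "stratified randomization according to the trial site and prior failure of a discontinuation attempt (yes/no").

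**Confirmatory tests.** Section 16.7 fixes them: "Null hypotheses 1, 2 and 4 will be tested with the two-sided, uncorrected chi-square test", and "Null hypothesis 3 will be tested with the two-sided log-rank test". The synopsis repeats both choices. Neither place gives a stratified or adjusted form. Section 16.1 adds: "All four hypotheses are tested at significance level 0.05", in a fixed order that stops at the first non-rejection.

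**Covariates.** Baseline variables enter only as exploratory work: "multivariate logistic or Cox regression analyses will be performed to analyse the influence of baseline covariates". The one example given there is the duration of earlier TKI therapy; prior failure is not named. Section 16.3 lists an earlier unsuccessful attempt among the baseline characteristics to be tabulated.

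**Sample size.** Section 16.10 uses the same unstratified chi-square test and arrives at 192 evaluable patients, 214 with 10% drop-out.

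**The concern.** Balancing the arms on a factor and then leaving it out of the analysis is a mismatch. If the factor predicts relapse, balanced allocation removes the between-stratum part from the real variability of the treatment difference, but the unstratified test still counts that part in its variance. The test then becomes somewhat conservative and less powerful than a stratified one.

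The margin is thin enough for this to deserve attention. Planned power is 80% to 83% at each fixed time and slightly above 80% for the log-rank test. A non-rejection at any step also ends confirmatory testing of every later hypothesis. Because the protocol itself names the tests, an analysis plan that stratified them would depart from it. The protocol does use stratification elsewhere: the biomarker Cox models in Section 16.7 are stratified for treatment group.

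**Working it through.** **1. Reproduce the plan's figures (unstratified chi-square, two-sided 0.05).**

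With p the mean of p1 and p2, n per arm = [1.96 × √(2p(1−p)) + 0.8416 × √(p1(1−p1) + p2(1−p2))]² / (p2 − p1)².

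For 45% vs 65%: [1.96 × √0.495 + 0.8416 × √0.475]² / 0.04 = (1.379 + 0.580)² / 0.04 = 95.9, so 96 per arm and 192 in total. 192 / 0.9 = 213.3, so 214.

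Power with 96 per arm = Φ{[0.20 × √96 − 1.96 × √(2p(1−p))] / √(p1(1−p1) + p2(1−p2))}:

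| Month | RFS, B vs A | Computed | Stated |
|---|---|---|---|
| 7 | 55% vs 75% | 83.3% | 83% |
| 13 | 50% vs 70% | 81.2% | 81% |
| 25 | 45% vs 65% | 80.0% | 80% |

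Sample size and planned test agree.

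**2. Why the unstratified test can be conservative.**

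Assume, for illustration, that a share f = 20% has a prior failure and that their RFS is d = 30 points lower, with 55% overall.

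- Total variance: 0.55 × 0.45 = 0.2475.
- Between-stratum part: f(1−f)d² = 0.16 × 0.09 = 0.0144.
- Within-stratum share: (0.2475 − 0.0144) / 0.2475 = 0.942.
- Under perfect balance the true size is about 2 × [1 − Φ(1.96 / √0.942)] = 4.3%.

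With f = 10% and d = 15 points, the between-stratum part is 0.09 × 0.0225 = 0.0020, the within-stratum share is 0.992, and the size is about 4.9%. The effect needs a strong factor.

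**3. Simulation, unstratified chi-square against Cochran-Mantel-Haenszel (CMH).**

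Settings: 96 per arm, perfect balance within the prior-failure stratum, a common treatment odds ratio, 200,000 runs per scenario. CMH = [Σ(x_A − E)]² / ΣV, summed over the two strata, with E = n_A·M/N and V = n_A·n_B·M(N−M) / [N²(N−1)], where M is the number relapse-free and N the number of patients in the stratum. Share and deficit are assumptions; the RFS rates come from Section 16.10.

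| Month | Share | Deficit | Size: chi-square / CMH | Power: chi-square / CMH |
|---|---|---|---|---|
| 7 | 20% | 0 points | 5.0% / 5.0% | 83.5% / 83.3% |
| 7 | 10% | 30 points | 4.7% / 4.8% | 83.9% / 84.8% |
| 7 | 20% | 15 points | 4.8% / 4.8% | 83.6% / 83.9% |
| 7 | 20% | 30 points | 4.3% / 4.8% | 84.3% / 85.7% |
| 7 | 30% | 30 points | 4.0% / 4.8% | 84.5% / 86.2% |
| 25 | 20% | 30 points | 4.3% / 4.9% | 80.9% / 82.4% |
| 25 | 30% | 30 points | 4.2% / 5.0% | 81.0% / 83.0% |

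With the prognostic effect put as an odds ratio of 1/2 to 1/5 and a share of 10-30%, still under perfect balance, the CMH gain is 0.2 to 2.8 points at month 7 and 0.1 to 3.4 points at month 25.

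**4. The allocation actually planned.**

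Blocks run within site and prior failure: about 20 × 2 = 40 cells, and 214 / 40 is about 5 patients per cell. At a 10-30% share, a site has about 1 to 3 prior-failure patients (214 × 0.10 / 20 = 1.1; 214 × 0.30 / 20 = 3.2). Many blocks stay incomplete, so balance on the factor is looser than in step 3. Simulating this with an assumed block size of 4 and the same odds ratios gives a gain of about 0.2 to 3 points at month 7 and 0.2 to 4 at month 25. The loss is at most about 0.3 points when the factor has no effect. The size of the chi-square test is then mostly 4-5%.

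**5. Log-rank test (H3).**

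Exponential times over 24 months after TKI stop, 45% vs 65%, a 10-30% share, a stratum hazard ratio of 2 to 3, idealised balance, 8,000 runs. The unstratified test has size 3.3-4.8%, and stratifying adds about 0.8 to 4.2 points (20% share, hazard ratio 3: 82.7% to 86.5%).

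**The case against.** The strongest reply is that nothing here is wrong. The sample size was calculated for the very test that will be used, the figures reproduce, and every simulated power for the unstratified test meets the stated value. A slightly conservative test cannot create a false claim. All of this stands.

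Three stronger readings are tempting, and the documents support none of them:

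- A reader might infer that ignoring the strata inflates the type I error or invalidates the tests. The error moves the other way, to at or below 5%.
- A reader might infer that the trial is underpowered, or that power built into the design is being lost. No stratified power was ever planned; the loss exists only relative to a better test.
- A reader might infer that the protocol regards prior failure as a predictor of relapse. It never says so. It admits these patients, requires the failure to be documented and stratifies on it, but gives no reason and no RFS figure for them. That the factor is prognostic is a reasonable inference, not a stated premise.

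Two further points also stand. Incomplete blocks make the conservatism less certain than perfect balance suggests. And dropping site while keeping prior failure is a judgement about sparse cells, not a strict rule that analysis must follow randomisation. The exploratory regressions could include prior failure, but they do not name it and are not confirmatory.

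**Conclusion.** The mismatch is real and stands in the protocol's own text; its consequence is limited to efficiency. The planned tests are valid, 192 evaluable and 214 randomised patients remain correct, and the stated power is met.

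If 10-30% of patients have a prior failure and its odds ratio for staying relapse-free is 1/2 to 1/5, stratifying adds roughly 0 to 3 points of power at month 7 and up to about 4 at month 25. The upper values need the strong end of that range, and so does a true size clearly below 5%. If the factor is not prognostic, almost nothing is lost. The range for H3 is similar but rests on exponential times and idealised balance.

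Share, odds ratio and block size are assumptions, since the protocol gives none of them. The point is a free improvement.

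**What to change.** Before the month-7 analysis, which Section 16.8 makes the test of H1, amend Section 16.7 and the synopsis and carry the same wording into the analysis plan:

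- H1, H2 and H4: two-sided Cochran-Mantel-Haenszel test at 0.05, stratified by prior discontinuation failure (yes/no) as recorded at randomisation.
- H3: two-sided log-rank test at 0.05, stratified by the same factor.
- No stratification by site in the confirmatory tests, with sparse cells (about 40 for 214 patients) given as the reason.
- The unstratified chi-square and log-rank tests reported as sensitivity analyses.

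The cost is wording only. The factor is already collected, and patient numbers, visits, the order of the hypotheses and their significance levels stay as they are.

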**Legend to table 1a and table 1b**

1. Visits can be pre- or postponed by 7 days.
2. Randomization could be done up to two working days prior to potential study treatment start. If the patient will not meet all the inclusion criteria / fulfill the exclusion criteria, or will withdraw his informed consent before the randomization, he/she must be registered by KKS Marburg using the Screening/Randomization form
3. A pre-mature end of treatment (EOT) assessment must be performed before months 15 for reasons outlined in section 13 and latest at the scheduled next visit. A regular end of treatment visit can be pre- or postponed by 10 days.  
**IMPORTANT:** a premature end of treatment, in case of molecular relapse (loss of MMR) or withdrawal of informed consent, irrespective of whether occurring in arms A or B requires to immediately resume TKI therapy. **After the premature EOT Visit has been performed, a molecular BCR-ABL follow up every three months until month 25 is required.** After month 25 off study follow ups will occur annually, as indicated in the flow chart.
4. Safety laboratory analysis should not be older than 7 days before start of study treatment with AOP2014 in arm A. If the Baseline Visit (V1) will not be performed within 1 week from Screening Visit, the safety laboratory analyses assessments have to be repeated on V1 for arm A. This includes: complete blood counts including differential blood count (machine), Na, K, Ca, Krea, Urea, GOT, GPT, AP, GGT, LDH, Bilirubine, total Protein, PT, PTT, Glucose (see 12.1.2 and 12.2.8).
5. BCR-ABL PCR must be performed at one of the two EUTOS-certified laboratories named in section 12.2.10: 20 – 30 ml blood are required.  
BCR-ABL PCR must have been confirmed three times with at least MR^4 please refer to inclusion criterium number 5.
6. For every visit HCG from serum only in Arm A in women of childbearing potential.  
Additional HCG urine test for home use > 28 days only in Arm A in women of childbearing potential.
7. For immune / stem cell marker 30ml (CD86+pDCs) of heparin and 5ml Serum are required (see 12.2.11). Shipment of samples to Marburg should be performed Monday-Thursday and is possible by regular mail.
8. For interferon alpha (IFN) response and adverse event prediction scores (see 12.2.11), please send 9 to 10 ml EDTA peripheral blood (PB) by regular mail to Aachen.

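### The month-25 window for hypothesis 4 runs to month 30.5, so a patient in MMR at month 25 who later dies or transforms is rated as relapsed at 25 months

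*Protocol*

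**What the plan says.** Section 16.1 words null hypothesis 4 for a fixed time: "The probability of molecular RFS 25 months after randomization / 24 months after stopping TKI is not different between the two arms A and B".

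Section 16.7 (primary efficacy endpoint) assigns PCR results to visits by a single rule: "intervals are defined by the time in the middle between two visits". For the first two time points, "the interval for relating a result to the 7-month visit is given by 6.5 to 7.5 months after randomization" and "the interval for relating a result to the 13-month visit is given by 12 to 14 months". For the last, "with visits foreseen 24, 25, and 36 months after randomization", it concludes that "the result should be recorded within the interval from 24.5 to 30.5 months after randomization". The same section adds: "In case of the observation of an extremely unfavourable result prior to the upper time limit of an interval, this result will be carried forward". Such a result is rated as loss of MMR or relapse. The results meant are accelerated disease, blast crisis and death from any cause. If several PCRs fall in one window, a cited method paper determines which one decides.

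Note 1 to the schedule tables reads: "Visits can be pre- or postponed by 7 days". After month 25, section 12.1.7 requires documentation only at months 36, 48 and 60, and merely recommends three-monthly PCR. Section 5 follows RFS at months 36, 48 and 60 in patients who were in treatment-free remission (TFR) at the end of month 25.

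**The concern.** Midpoints work while visits are close together. After month 25 the next contact is eleven months away and off study, so the window reaches 5.5 months past its target. The 7-day tolerance needs almost none of that.

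The carry-forward rule is tied to the upper limit of the window, so the extra months count. Death or transformation before month 30.5 overrides a PCR showing MMR at month 25. Section 5 would place the same patient in the cohort in TFR at month 25 and count the event against month 36. The two parts of the protocol thus classify one patient in two ways.

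The stretch is also not systematically observed. No study documentation is scheduled between months 25 and 36, and section 14.5 limits serious-event reporting after month 15 (arm B) or 16 (arm A) to reactions related to study medication. Section 16.7 evaluates the secondary endpoints, which include 25-month RFS, once 25-month follow-up has been collected. At that point patients recruited late may still have open windows.

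At stake is whether a confirmatory test answers the question in its hypothesis, and whether its data are gathered alike for all patients.

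**Working it through.** **1. The plan's windows, reproduced**

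| Target | Neighbouring visits | Midpoints | Offset from target |
|---|---|---|---|
| 7 | 6, 8 | 6.5, 7.5 | -0.5/+0.5 |
| 13 | 11, 15 | 12, 14 | -1/+1 |
| 25 | 24, 36 | (24+25)/2 = 24.5; (25+36)/2 = 30.5 | -0.5/+5.5 |

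The stated 24.5-30.5 follows exactly from the rule. It is not a typing error.

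**2. What the visit tolerance needs.** 7 days is 7/30.4 = 0.23 months, so month-25 visits fall between 24.77 and 25.23. A window of 24.5-25.5 holds all of them.

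**3. One patient traced.** MMR at month 25, death at month 29. Section 16.7: 29 < 30.5, so relapse for hypothesis 4. Section 16.1: relapse-free at 25 months. Section 5: in TFR at month 25, failure at month 36.

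**4. Who can be reclassified.** Only patients still relapse-free at month 25. With section 16.10's 96 evaluable per arm and RFS of 45% and 65%: 96 × 0.45 = 43.2 and 96 × 0.65 = 62.4, together 105.6 of 192, or 52.8 per arm on average.

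**5. Reclassified deaths.** Exposure is 30.5 - 25.2 = 5.3 months. The protocol gives no mortality, so 0.5-2% per year is assumed.
- 105.6 × 0.005 × 5.3/12 = 0.23
- 105.6 × 0.02 × 5.3/12 = 0.93

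That is 0.12 to 0.47 per arm on average. No rate is assumed for transformation; section 2.5 asserts that there is no risk of progression after stopping TKI.

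**6. Late PCRs.** Assumed late relapse rate 2-10% per year:
- 52.8 × 0.02 × 5.3/12 = 0.47 per arm
- 52.8 × 0.10 × 5.3/12 = 2.33 per arm

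These are all relapses in the stretch. One enters hypothesis 4 only if the patient has no PCR near month 25, or if the cited multiple-result method selects the late value; that method cannot be checked here. If 5-10% of patients have only a late PCR (assumed), the count is 0.47 × 0.05 = 0.02 to 2.33 × 0.10 = 0.23 per arm.

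**7. Total per arm.** 0.12 + 0.02 = 0.14 to 0.47 + 0.23 = 0.70 patients, or 0.1 to 0.7 percentage points of 96. For arm A alone at the upper rates: 62.4 × 0.02 × 5.3/12 + 62.4 × 0.10 × 5.3/12 × 0.10 = 0.55 + 0.28 = 0.83, still under one patient.

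**8. Effect on the test.** Two-sided uncorrected chi-square, 96 per arm; power at 45% vs 65% is 80.0%, as stated. If RFS were read at 30.5 months in everyone:
- 13-to-25-month event rate continues: 0.45 × (0.45/0.50)^(5.5/12) = 42.9% vs 0.65 × (0.65/0.70)^(5.5/12) = 62.8%; power 79.5%.
- Exponential hazard continues: 0.45^(30.5/25) = 37.8% vs 0.65^(30.5/25) = 59.1%; power 84.8%.

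Near the threshold one patient matters. With 43/96 relapse-free in arm B, 57/96 in arm A gives p = 0.043 and 56/96 gives p = 0.060.

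**9. Calendar.** Last patient out is at 18 + 25 = 43 months, but that patient's window closes at 18 + 30.5 = 48.5 months.

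**The case against.** The rule is pre-specified, applied consistently and identical in both arms. It ensures that each result belongs to exactly one visit, and a wide last window rescues patients who attend late. The month-25 PCR is scheduled and obligatory, so for most patients hypothesis 4 does read status at month 25. Section 16.10 expects hardly any molecular relapse after 25 months, and section 2.1.4 reports a discontinuation study with none after 24 months. Only the last step of the hierarchy is touched.

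Most of this stands, and it limits the size of the point. It also rules out three stronger readings that a reader might infer:
- That late PCRs generally decide 25-month status. They do so only without a PCR near month 25, or if the cited method selects them.
- That the window shifts an arm's RFS by 2-3 percentage points. That needs every patient to miss the month-25 PCR at the highest assumed rates: (2.33 + 0.47)/96 = 2.9%.
- That the rule favours one arm or damages power. Late events in both arms leave power at 79.5-84.8%.

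The objection does not answer the carry-forward rule. Applying it alike to both arms does not turn a death at month 29 into a relapse at month 25, and that classification overrides a PCR already in hand.

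**Conclusion.** The point holds as a defect in how hypothesis 4 is defined and how its outcomes are ascertained. Its expected numerical effect is small. As written, death, accelerated phase or blast crisis up to 5.5 months after the time point is charged to 25-month RFS, against section 16.1 and the month-25 cohort in section 5, over months with no scheduled documentation.

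The size is about 0.2 to 0.9 reclassified deaths over both arms, plus a small fraction of 0.5 to 2.3 late relapses per arm. That is under about one patient per arm unless many month-25 PCRs are missed. It rests on assumed mortality (0.5-2% per year), late relapse (2-10% per year) and late-only PCRs (5-10%), none of which the protocol gives.

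The 7-month primary test and hypothesis 2 have their own symmetric windows. Hypothesis 3 uses event times, and the sample size of 192 evaluable and 214 randomized stands. The change is still worth making: hypothesis 4 is confirmatory, one patient can decide it, and the correction costs almost nothing.

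**What to change.** In section 16.7:
- Set the month-25 interval to 24.5-25.5 months.
- For hypothesis 4, carry death, accelerated phase or blast crisis forward only if it occurs by month 25.5.
- Use a PCR from 25.5-30.5 months only for patients with none in 24.5-25.5. A value of at most 0.1% off TKI counts as relapse-free at 25 months. A first value above 0.1% counts as relapse in the main analysis, with a sensitivity analysis that treats it as relapse-free or as missing at month 25.

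The cost is a wording change and one sensitivity analysis, with no new visits or patients. The downside is that a few late attenders still have an uncertain 25-month status; the sensitivity analysis shows whether they matter.
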